**Figure 4 figure4:**
[figure not shown]
Screenshot of Kinovea 2D motion analysis software.

#### Balance

The one-leg standing balance test will be evaluated with eyes open and closed [23]. The participant lifts one foot with eyes open so that it does not touch the support leg and tries to maintain this position. The individual is expected to maintain this position for a maximum test duration of 30 seconds. The time he remains on one leg will be recorded.

#### Functional Capacity

The 6MWD test will be applied for the evaluation of functional capacity. The patient is asked to walk as far as possible at their own walking pace for 6 minutes in a 30-meter straight corridor. Before starting the test, the patient rests in a sitting position for 10 minutes in the corridor where the test will be performed. At the end of the test, 6MWD is recorded in meters [24].

#### Proprioception

A digital goniometer will be used to assess proprioception. Proprioception assessment will be performed for knee and ankle joints. During the knee joint assessment, the patient will be positioned from the bed with feet hanging down and knees in 90° flexion. The pivot of the digital goniometer will be placed on the lateral condyle of the femur, and the knee will be brought to the previously determined 15° and 30° extension angles. The patient will be asked to perceive the position of this angle by waiting for 10 seconds with eyes open. Then, the patient will be asked to actively repeat these angles 3 times for both knees with eyes closed. For ankle proprioception measurement, the patient will be placed in a long sitting position on the bed. A neutral position will be provided for the ankle; the lateral malleolus of the fibula will be taken as the pivot point and the goniometer will be placed on the pivot point. The fixed arm of the goniometer will be kept parallel to the lateral midline of the fibula, and the movable arm will be placed to follow the lateral midline of the 5th metatarsal bone. The goniometer will be brought to an angle of 20°, and the patient will be asked to make a plantar flexion movement of the ankle and hold it at this angle for 5 seconds with the eyes open. Then, the patient will be asked to return to the starting point and find the target angle, that is, the range of motion of 20°, with the eyes closed. The measurement will be repeated 3 times for both ankles with the same method [25].

#### Functional Independence

The Functional Independence Score in Hemophilia has been developed as an assessment tool used to measure the functional ability of the patient with hemophilia. The patient is asked to score their level of independence in 8 activities under 3 main headings related to activities of daily living. These activities are eating or self-care, bathing, dressing, transfers, squatting, walking, climbing stairs, and running. The patient will be asked questions and asked to score between 1 and 4. The total score will be recorded [26].

### Intervention

All participants will be divided into 3 groups. Group 1 is the closed kinetic exercise group, group 2 is the proprioceptive exercise group, and group 3 is the control group. Participants in group 1 and group 2 will receive exercise training twice a week for 12 weeks for a total of 24 sessions of 45 minutes each. The control group will not receive any intervention. Exercise training will continue under the supervision of the physiotherapist. Patients will have completed their factor replacement on the day of exercise. If any signs of bleeding are observed, the exercise session will be terminated. Following randomization, all participants in exercise training groups will receive a 30-minute education session on joint protection techniques and energy conservation prior to the first exercise session. This training will cover the goals and basic principles of joint and energy education; correct and incorrect posture characteristics; proper standing, sitting, and lifting techniques; the benefits of correct posture; posture recommendations for different activities; hand protection methods; factors contributing to fatigue; and basic principles of energy management.

### Closed Kinetic Chain Exercise Training

Group 1 exercises will start with a 5-minute warm-up. The warm-up exercises include marching in place, shoulder circles, elbow stretching, seated knee flexion and extension, as well as stretching exercises targeting the hamstring and gastrocnemius muscles. Thereafter, 6-8 different closed kinetic chain exercises will be planned as 2-3 sets and 8-10 repetitions (Figure 5). Subsequently, the session will be finished by cooling down for 5 minutes and applying ice to the lower extremity joints for 15 minutes. Each session is expected to last approximately 40-45 minutes. Exercises will be progressively made more difficult once every 2 weeks. Exercise training will continue under the supervision of a physiotherapist 2 days a week for 12 weeks. The details of the closed kinetic chain exercise training and progression are given in Table 1.

**Figure 5 figure5:**
[figure not shown]
Examples of closed kinetic chain exercises. (A) Terminal knee exercise with resistance band. (B) Single leg bridge exercise.

**Table 1 table1:** Closed kinetic chain exercises protocol.

			Repetitions (n)		Sets (n)
**Weeks 1-3**					
	Terminal knee extension (both sides)	10		2	
	Bridge	10		2	
	Bridge with hip adduction	10		2	
	Lunge (both sides)	10		2	
	Side lunge (both sides)	10		2	
	Mini squat	10		2	
	Step up (both sides)	10		2	
**Weeks 4-6**					
	Terminal knee extension (both sides)	10		3	
	Bridge	10		3	
	Bridge with hip adduction	10		3	
	Lunge (both sides)	10		3	
	Side lunge (both sides)	10		3	
	Mini squat	10		3	
	Step up (both sides)	10		3	
**Weeks 7-9**					
	Terminal knee extension with mild resistance band (both sides)	10		2	
	Bridge with mild resistance band	10		2	
	Single leg bridge	10		2	
	Lunge (both sides)	10		2	
	Side lunge (both sides)	10		2	
	Mini squat on unstable surface	10		2	
	Mini squat with hip adduction (both sides)	10		2	
**Weeks 10-12**					
	Terminal knee extension with mild resistance band (both sides)	10		3	
	Bridge with mild resistance band	10		3	
	Single leg bridge	10		3	
	Lunge (both sides)	10		3	
	Side lunge (both sides)	10		3	
	Mini squat on unstable surface	10		3	
	Mini squat with hip adduction(both sides)	10		3	

### Proprioceptive Exercise Training

Proprioceptive exercise training will focus on sensorimotor training. In this training model, vibration training, reposition exercises, and proprioception exercises will be given to increase proprioceptive input (Figure 6).

Exercise training will start with the same 5-minute warm-up as in the closed kinetic chain exercise group and will continue with vibration application to the knee and ankle joints. Since damage or loss of mechanoreceptors due to degenerative events in the joint in people with hemophilia may adversely affect the balance and proprioception required in activities, there may be a decrease in lower extremity vibration sensation [27].

Vibration training will be applied to 4 points, that is, patellar tendon, medial knee joint, lateral knee joint (medial collateral ligament and lateral collateral ligament), and the upper part of the patella bone. The application to each point will start with 30 seconds, and the application time will be increased by adding 15 seconds every 2 weeks.

Then reposition exercises will be started. Kinetic reposition exercises will be performed on 3-way lines drawn on a white cardboard paper. One of the lines drawn on the white cardboard is straight, and the other 2 are lines drawn at 30° angles to the straight line, considering that the internal and external (axial) rotation of the tibia on the femur is 45° when the knee is at 90°. Numbers in centimeters will be written on the lines. The patient will be seated on the chair with 90° knee flexion and will be asked to put his or her foot on these lines and hold it for 10 seconds to take his or her foot to the point 10 cm away and learn that point. Afterwards, the patient will return to the starting point and will be asked to find the point he or she learnt with his or her eyes closed.

The program will be planned as 6-8 different proprioceptive exercises performed in 2-3 sets and 8-10 repetitions. Finally, the session will be finished by cooling down for 5 minutes and applying ice to the lower extremity joints for 15 minutes. Each session is expected to last approximately 40-45 minutes. Exercises will be progressively made more difficult once every 2 weeks. The details of proprioceptive exercise training and progression are given in Table 2.

**Figure 6 figure6:**
[figure not shown]
Examples of proprioceptive exercises. (A) Standing on a Bosu ball. (B) One-leg stand on a foam surface.

**Table 2 table2:** Proprioceptive exercises protocol.

		Duration or repetition (min or s)	Sets (n)
**Weeks 1-3**			
	Warm-up	5 min	N/A^a^
	Application of vibration (patellar tendon, medial, and lateral sides of the knee joint; both sides)	30 s	N/A
	Kinetic repositioning exercises (both sides)	All directions	5
	Standing on a balance board	10 s	2
	Standing on a Bosu ball	10 s	2
	One-leg stand	10 s	2
	Semitandem walking	10 s	3
	Cool down	5 min	N/A
**Weeks 4-6**			
	Warm-up	5 min	N/A
	Application of vibration (patellar tendon, medial, and lateral sides of the knee joint; both sides)	45 s	N/A
	Kinetic repositioning exercises	All directions	5
	Standing on a balance board	10 s	3
	Standing on a Bosu ball	10 s	3
	One-leg stand	10 s	3
	Semitandem walking	30 s	2
	Cool down	5 min	N/A
**Weeks 7-9**			
	Warm-up	5 min	N/A
	Application of vibration (patellar tendon, medial, and lateral sides of the knee joint; both sides)	60 s	
	Kinetic repositioning exercises (both sides)	All directions	10
	Eyes open and close standing on a balance board	15 s	2
	Eyes open and close standing on a Bosu ball	15 s	2
	Eyes closed one-leg stand	15 s	2
	One-leg stand on foam surface	15 s	2
	Tandem standing	15 s	2
**Weeks 10-12**			
	Warm-up	5 min	N/A
	Application of vibration (patellar tendon, medial, and lateral sides of the knee joint; both sides)	60 s	N/A
	Kinetic repositioning exercises (both sides)	All directions	10
	Eyes open and close standing on a balance board	20 s	3
	Eyes open and close standing on a Bosu ball	20 s	3
	Eyes closed one-leg stand	20 s	3
	One-leg stand on foam surface	20 s	3
	Tandem standing	20 s	3

^a^N/A: not applicable.

### Statistical Analysis

Data will be statically analyzed using SPSS (version 25.0; IBM Corp). Normality tests (visual and analytical) will be applied. Descriptive statistics will be presented as mean (SD) or frequency (percentage). The Shapiro-Wilk test will be used to assess the normality of data distribution. For normally distributed data, a one-way analysis of variance test will be applied for between-group comparisons, and a 2-sided paired sample *t* test will be used for within-group changes. For nonnormally distributed data, the Kruskal-Wallis test will be used for between-group comparisons, and the Wilcoxon test will be applied for within-group changes. In cases where between-group comparisons of normally distributed data show significant results, Tukey or Bonferroni corrections will be used as post hoc analyses to identify the source of the differences. For nonnormalized distributed data, Mann-Whitney *U* tests will be conducted for between-group comparisons. A *P* value <.05 will be considered statistically significant for all analyses.

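### A normality check on the trial's own final data decides whether each outcome, including the four primaries, is compared on means or on ranks

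*Protocol article*

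**What the plan says.** All of this is in the Statistical Analysis section of the protocol article.

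- How normality is judged: "Normality tests (visual and analytical) will be applied", and "The Shapiro-Wilk test will be used to assess the normality of data distribution".
- If judged normal: "For normally distributed data, a one-way analysis of variance test will be applied for between-group comparisons", with paired t tests within arms. After a significant result, "Tukey or Bonferroni corrections will be used as post hoc analyses to identify the source of the differences".
- If judged non-normal: "For nonnormally distributed data, the Kruskal-Wallis test will be used for between-group comparisons", with Wilcoxon tests within arms and Mann-Whitney tests between pairs of arms.
- Threshold: a P "value <.05 will be considered statistically significant for all analyses".

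The Outcome Measures section lists four primary outcomes: sway in two directions, gait speed and the joint health score. No section assigns any of them a test. The Results section says analysis begins only after every enrolled participant has finished treatment, so normality is judged on the final outcome data.

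**The concern.** ANOVA compares means and Kruskal-Wallis compares ranks, so the two tests answer different questions. Under this rule the trial learns which question it asked of each primary outcome only after seeing the data. One primary outcome may be reported on means and the next on ranks because of sampling variation in a pretest with about 18 values per arm. The rank route names no estimate of the treatment difference in outcome units, which is what a reader needs when comparing two exercise programmes. The article states the data-driven rule outright, so this is not a detail merely left to a fuller document.

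The rule also chooses between two tests neither of which takes the baseline value as a covariate. The Abstract says the initial measurements are repeated after treatment, so that value will be available for every outcome.

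**Working it through.** **Inputs from the article.** 18 evaluable per arm, three arms, 21 enrolled per arm (Participant Selection); four primary outcomes (Outcome Measures); .05 for all analyses (Statistical Analysis). The enrolment figures agree: 3 × 21 = 63, and going from 18 to 21 allows 3/21 = 14.3% loss. The 18 cannot be recomputed because the effect size is not printed. Nothing below depends on that.

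**Assumptions not in the article.** Shapiro-Wilk at .05; applied either once to pooled data or once in each arm; outcomes independent where stated; skewed outcomes log-normal with log-SD 0.25 to 0.6; a true benefit of 0.8 SD in both exercise arms where power is discussed; baseline correlation 0.6. Simulations used 3,000 to 6,000 trials per setting.

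**Step 1. A truly normal outcome sent to ranks by chance.**
- One pooled check: 5%.
- One check per arm: 1 − 0.95³ = 14.3% (simulated 14.0% at 18 per arm, 14.5% at 21).

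**Step 2. At least one of four primary outcomes so sent, under independence.**
- Pooled: 1 − 0.95⁴ = 18.5%.
- Per arm: 1 − 0.95¹² = 46.0%.

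**Step 3. Skewed outcomes.** With a check in each arm, 43%, 71% and 93% of trials go to ranks at log-SD 0.25, 0.4 and 0.6. With mild to moderate skew, the same underlying distribution takes either route.

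**Step 4. Type 1 error of the three-arm comparison.**

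| Rule | Simulated error |
|---|---|
| ANOVA always | 4.6%–5.6% |
| Kruskal-Wallis always | 4.6%–5.4% |
| Gated rule, followed mechanically | 5.0%–5.7% |
| Better of the two tests taken | 5.8%–7.2% |

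**Step 5. How often the gate changes the verdict against ANOVA always.** With the benefit as a constant shift:

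| Outcome shape | Verdict differs | Power, ANOVA always | Power, gated |
|---|---|---|---|
| Normal | 1.1% | 67.6% | 67.3% |
| Log-SD 0.25 | 4.9% | 67.8% | 71.1% |
| Log-SD 0.4 | 11.2% | 69.0% | 78.3% |

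At log-SD 0.6 the difference is about 14% if the benefit is proportional to the participant's value, and about 20% if it is a constant shift.

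**Step 6. What baseline adjustment would add.** With correlation 0.6, the relative variance is 1 for the follow-up value, 2(1 − 0.6) = 0.80 for the change, and 1 − 0.6² = 0.64 for the baseline-adjusted value. With a proportional benefit and follow-up values compared, the gated rule has about 65% to 69% power and the baseline-adjusted linear model about 79% to 86%, both with type 1 error near 5%. If changes were compared instead, the gap would be smaller.

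The gain is not universal. With a constant shift at log-SD 0.6, the gated rule reached about 90% and the untransformed adjusted model about 84%. That is a reason to settle any transformation beforehand.

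**The case against.** The strongest reply is that the plan does fix something: a conditional rule with a named test and both branches written down. Two-stage choices of this kind are common. Followed mechanically, the rule costs almost nothing in type 1 error, changes about 1% of verdicts on normal data, and gains power over raw-scale ANOVA on skewed data with a constant shift. All of that stands, and it limits the size of the point. It does not answer the point itself, because a rule that picks between means and ranks on the final data still leaves the compared quantity open.

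Several stronger readings are tempting, and the article does not support them.

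- **That false positives are materially inflated.** Step 4 shows otherwise. Even free choice of the better test gives only about 6% to 7%, and that would depart from the written rule.
- **That 46% is the chance of a false switch.** It needs a check in each arm and four independent outcomes. The article states neither, and both sway measures come from the same Biodex assessment.
- **That the gate reverses 7% to 12% of results.** In the 0.8 SD scenario that is how often ANOVA and Kruskal-Wallis disagree, not how often the gate changes the verdict.
- **That the article errs by not saying which check prevails, or whether raw values or residuals are checked, pooled or by arm.** A fuller analysis plan may hold such details.
- **That the capped one-leg stand shows an error.** The sentence "The individual is expected to maintain this position for a maximum test duration of 30 seconds" only describes a secondary outcome.

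**Conclusion.** The point holds as a weakness of moderate size that is worth correcting. The article lets a pretest on the final data decide whether each primary outcome is compared on means or ranks. By chance alone a normal outcome goes to ranks in 5% to 14% of trials, and at least one of four does so in 18.5% to 46% under an independence assumption that is doubtful here. The gated verdict differs from that of fixed ANOVA in about 1% of trials on normal data. On skewed data with a 0.8 SD benefit it differs in about 5% to 14%, and in more only for strong skew combined with a constant shift. Omnibus type 1 error stays near 5% to 6%, so a reader should not infer that the trial's error control fails.

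The real losses are a comparison not fixed in advance, no effect estimate named on the rank route, and no baseline covariate on either route. The percentages rest on 18 per arm, Shapiro-Wilk at .05 and the assumed outcome shapes. The reading of the rule rests on the article's text alone.

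**What to change.** Before analysis starts, remove the normality check as the selector of the test and name one method for each primary outcome: a linear model of the week-12 value on arm and baseline value, reporting between-arm differences with 95% CIs. If a transformation is wanted for any outcome, state it in the same text, before the data are examined. Keep residual plots and a rank analysis as labelled sensitivity analyses that cannot replace the primary result.

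This takes a few sentences, with no new data and no change in sample size. The small downside is that the model is kept when residuals are mildly non-normal, which the sensitivity analysis would show. Timing matters: the Results section reports 34 participants through treatment by April 2025 and expects completion in May 2025, so the change should be dated and made before outcome data are examined.

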**Methods:**

This study is a 3-arm, parallel-group randomized controlled trial with 63 people with hemophilia aged 13-25 years who meet the inclusion criteria. The primary outcome measures are medio-lateral swing, anterior-posterior swing, walking speed, and Hemophilia Joint Health Score. Secondary outcome measures are kinematic assessment of gait, one-leg stand test, 6-minute walk distance (6MWD) test, proprioception assessment, and the Functional Independence Score in Hemophilia. Participants will be evaluated with the Biodex balance system for postural sway, 10-meters walking test for gait speed, Hemophilia Joint Health Score for joint health, Kinovea 2D motion analysis for kinematic evaluation of gait, one-leg stand test for balance measurement, 6MWD for functional capacity, digital goniometer for proprioception, and Functional Independence Score in Hemophilia for functional independence. Participants will be randomly assigned to a closed kinetic chain exercise group, a proprioceptive exercise group, or a control group. All participants in exercise training groups will receive a 30-minute education session on joint protection techniques and energy conservation prior to the first exercise session. Closed kinetic chain exercises will include progressive lower limb exercises of approximately 45 minutes each session. Proprioceptive exercise training will focus on vibration training; reposition exercises and proprioception exercises will be administered to increase proprioceptive input for the same duration as the other group. The control group will receive no intervention. All participants will undergo 24 exercise sessions (2 days a week for 12 weeks). After the treatment, the initial measurements will be repeated.

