**Conclusions:**

This study will investigate the effects of 2 different exercises on functional parameters in people with hemophilia. The effects of different exercise protocols on parameters such as postural sway, walking speed, and joint health will be evaluated. It is predicted that both exercise methods may have positive effects on balance and gait.

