## Methods

### Participant Selection

The sample size was calculated as 18 individuals for each group using the G*Power program (version 3.1.9.4; Heinrich Heine University) with 90% power and .05 type 1 error using the medio-lateral swing effect size value as reference in the balance assessment in the study by Tat et al [19]. Considering that there might be individuals who would not complete the study, a total of 63 participants, that is, 21 individuals for each group, will be included.

The inclusion criteria of the participants in this study were as follows: (1) diagnosed with hemophilia A and hemophilia B, (2) have a blood factor level below 5%, (3) is 13-25 years of age, (4) have a history of bleeding in the lower extremities, (5) have a target joint, (6) have a total lower extremity Hemophilia Joint Health Score ≥3, and (7) is receiving prophylaxis (factor support to prevent bleeding). The exclusion criteria were as follows: (1) individuals having undergone lower extremity surgery in the last 6 months, (2) having BMI>30 kg/m^2^, (3) having an inhibitor, (4) using a walking aid, and (5) being involved in any physiotherapy or exercise program in the last 6 months.

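### The between-arm ANOVA is valid but has no baseline covariate, although baseline is measured; ANCOVA would gain precision at almost no cost, and the within-arm tests should be descriptive only

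*Protocol article*

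**What the plan says.** In the Statistical Analysis section of the protocol article, the arms are compared as follows: "a one-way analysis of variance test will be applied for between-group comparisons". For change inside an arm, "a 2-sided paired sample *t* test will be used for within-group changes". The non-normal route has the same structure: "the Kruskal-Wallis test will be used for between-group comparisons, and the Wilcoxon test will be applied for within-group changes". Significant ANOVA results are followed by Tukey or Bonferroni comparisons, and Mann-Whitney tests serve the non-normal case. One threshold covers everything: "A *P* value <.05 will be considered statistically significant for all analyses".

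Baseline values are available. The Abstract (Methods) says: "After the treatment, the initial measurements will be repeated". No covariate, ANCOVA, mixed model or group-by-time term is named. The word for change is attached only to the within-arm tests, and the variable that enters the ANOVA is not stated.

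The Abstract (Conclusions) anticipates the result: "It is predicted that both exercise methods may have positive effects on balance and gait". The sample size in Participant Selection is 18 per arm, raised to 21 for dropout, and was computed "with 90% power and .05 type 1 error using the medio-lateral swing effect size value as reference". The effect size is not given as a number.

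**The concern.** A one-way ANOVA has one factor and no covariate. On post-treatment values it leaves the baseline unused. On change scores it uses the baseline only by subtraction, which is generally less precise than regression on it. With simple randomization and about 18 to 21 patients per arm, chance baseline differences add noise that a covariate would largely remove.

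The second part is about inference. A paired test inside an exercise arm responds to anything that moves scores over 12 weeks, including practice on repeated balance tests. Regression to the mean is also possible, because entry requires that patients "have a total lower extremity Hemophilia Joint Health Score ≥3" and the Hemophilia Joint Health Score is then a primary outcome. The untreated control arm exists to remove such shared change, and a within-arm test makes no use of it. Since these tests share the P<.05 threshold with the between-arm tests, and the article does not say which kind carries the efficacy conclusion, significant within-arm results could be reported as benefit without a difference from control.

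**Working it through.** **Inputs from the article.** 18 per arm, three arms, 90% power, type 1 error .05; Tukey or Bonferroni post hoc comparisons; outcomes measured before and after.

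**Assumptions, not in the article.** Baseline-to-post correlation r = 0.3 to 0.7; standardized pairwise difference d = 0.8 on the post-value scale; a shift common to all arms of 0.1 to 0.5 SD; equal SD before and after.

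**The plan's own figure.** The 18 per arm cannot be reproduced forward, because effect size, test family and sidedness are not given. Solved backwards at 90% power, it implies d of about 1.11 for a two-sided two-sample t test, or f of about 0.50 for a three-arm ANOVA.

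**Residual variance.** Relative to post values, ANCOVA leaves 1 − r². At r = 0.3, 0.5, 0.6, 0.7 this is 0.91, 0.75, 0.64, 0.51. Change scores have variance 2(1 − r) times that of post values, so ANCOVA relative to change is (1 − r²)/(2(1 − r)) = (1 + r)/2 = 0.65, 0.75, 0.80, 0.85.

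**Pairwise power.** Noncentral t with noncentrality d*·√(18/2) = 3d*. Here d* = d for post values, d/√(2(1 − r)) for change and d/√(1 − r²) for ANCOVA. Error df = 3×18 − 3 = 51, or 50 for ANCOVA. At d = 0.8 and r = 0.5, for example, ANCOVA has d* = 0.8/√0.75 = 0.924. Bonferroni uses .05/3.

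| d = 0.8, n = 18 per arm | r = 0.3 | 0.5 | 0.6 | 0.7 |
|---|---|---|---|---|
| Post values, unadjusted alpha | 65% | 65% | 65% | 65% |
| Change scores, unadjusted alpha | 51% | 65% | 75% | 86% |
| ANCOVA, unadjusted alpha | 69% | 78% | 84% | 91% |
| Post values, Bonferroni | 48% | 48% | 48% | 48% |
| ANCOVA, Bonferroni | 52% | 62% | 70% | 81% |

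**At the implied effect.** With d about 1.11, unadjusted post-value power is already 90%.

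**Overall three-arm test.** Noncentral F, with f/√(1 − r²) for ANCOVA. At f = 0.40 the ANOVA on post values has 73% power; ANCOVA has 77%, 85%, 90% and 96% at the four values of r.

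**Fewer completers.** Results reports 34 participants through treatment by April 2025, with completion expected in May 2025. If the trial closed near 34/3, about 11 per arm (a scenario, not something the article says), f of about 0.50 would give 68% on post values, against 81%, 87% and 94% with ANCOVA at r = 0.5, 0.6 and 0.7.

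**Within-arm tests with no exercise effect.** Let every arm change by s SD. The paired effect is s/√(2(1 − r)), tested two-sided with n = 18. With p the chance that one arm is significant, both exercise arms are significant and control is not with probability p²(1 − p).

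| Common shift s | r | p, each arm | Both exercise arms significant, control not |
|---|---|---|---|
| 0.1 | 0.5 | 7% | 0.4% |
| 0.3 | 0.5 | 22% | 3.9% |
| 0.3 | 0.7 | 34% | 7.7% |
| 0.5 | 0.5 | 52% | 13% |
| 0.5 | 0.7 | 73% | 14% |

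The last column cannot exceed 4/27 = 14.8%, reached at p = 2/3. In simulation with a common shift, the between-arm ANOVA stayed at about 5%, on post values and on change alike.

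**The case against.** The strongest reply is that nothing here is invalid. Under randomization a one-way ANOVA keeps its 5% error rate, and chance baseline imbalance is already allowed for in that rate: it costs variance and causes no bias. This stands, and it sets the grade of the point.

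Several stronger readings are tempting, and the article does not support them:

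- *The baseline is ignored altogether.* The ANOVA's dependent variable is unstated. If it is change, the baseline enters by subtraction, and at d = 0.8 and r = 0.7 the gap to ANCOVA is 86% against 91%, not 65% against 91%.
- *The trial is underpowered because of this.* If the true effect is what 18 per arm implies, unadjusted power is already 90%. The value d = 0.8 is an assumption, and at r = 0.3 the gain over post values is only 4 points.
- *Within-arm results will decide efficacy.* No passage says so. The predictions are hedged, between-arm tests with post hoc comparisons are planned, and the Discussion commits to comparing the two exercise programs. Reporting within-arm change is not itself a fault.
- *A false finding is likely in over a third of null trials.* At least one exercise arm significant with control not does occur in 37% of trials at a 0.3 SD shift and r = 0.7. But the prediction concerns both exercises; for both, with control not significant, the figure is 7.7%. The shift itself is assumed.
- *Regression to the mean is established.* The entry cut is low and applies to the lower-extremity score, whereas the outcome described has a maximum of 124. How strongly the cut selects on measurement noise is unknown.

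What survives is that ANCOVA beats both versions of the ANOVA at every r tabulated, and that the article does not say which tests carry the efficacy claim. The article fixes these methods itself, so they are not details left to an unseen analysis plan.

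**Conclusion.** The point holds as an efficiency gain with an inference safeguard: recommended, not a must-fix. The planned between-arm test is valid but less precise than the collected data allow. At an assumed d of 0.8 with 18 per arm, ANCOVA adds about 4 to 26 percentage points of unadjusted pairwise power over post values, and about 5 to 18 points over change scores, for r between 0.3 and 0.7. The gain matters most if the true effect is smaller than the sample size implies or if fewer patients complete; it is small when r is low.

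The within-arm tests cannot show that exercise works. Under a purely shared shift of 0.1 to 0.5 SD (r = 0.5 to 0.7), each arm is significant in 7% to 73% of trials, and both exercise arms without control in 0.4% to 14% of the tabulated cases. A reader might infer that the plan intends such claims; the article neither says so nor rules it out. The correlation, the effect size and the shift are all assumptions.

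**What to change.** For each outcome, fit ANCOVA with the post-treatment value as response and arm plus the baseline value of that outcome as predictors. Keep the planned multiplicity correction for the pairwise contrasts. Report adjusted differences with 95% CIs for each exercise arm against control and for one exercise against the other. If residuals are clearly non-normal, use a rank-based or permutation version of the same model.

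Report within-arm changes as mean change with 95% CI and no P value, and add one sentence saying that efficacy conclusions rest on between-arm contrasts only.

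The cost is a change of wording and one degree of freedom per outcome, with no new data. The Results section says that analysis starts only once all enrolled participants have finished treatment, so on the article's account the change can be made and dated beforehand.
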